### Sample size determination

The analysis is following a hierarchical testing procedure. In a first step, intervention 2 (student smoking prevention circuit plus parent intervention) will be compared to the control group with regard to the primary outcome (proportion of regular smokers at 24 months). Only if step 1 is significant at the 5% level (two-sided), will step 2 be tested confirmatively (otherwise all following analyses will be considered explorative). The second step involves two hypotheses: Intervention 1 (student smoking prevention circuit) compared to control; and Intervention 2 compared to Intervention 1, each with regard to the primary outcome. The sample size determination is based on the second step (having a smaller assumed intervention effect, thus requiring a higher sample size than step one) with the two hypotheses tested equally (significance level alpha 0.025 each). Taking into account the cluster design with an assumed intra-cluster correlation coefficient for schools (ICC) of 0.001 and a power of 80%, 15 (14.7 and 13.3 precisely for the two hypotheses) schools (=clusters) are required in each of the three arms to detect a 5% difference in the proportion of regular smokers after two years (assumptions: intervention 1: 30%, intervention 2: 25%, and control group: 35%). Since we assume on average 60 participating students per school, this yields a total of 15 × 3 × 60 = 2700 required students. Assuming a drop-out rate of about 20% this yields a targeted sample size of n = 3375 students to be randomized.

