### Statistical analysis

In general, multi-level regression models (Generalized Linear Mixed Models (GLMM)) with cluster effects (school and class within school) will be used for all statistical analyses. For the primary analysis, a logit model will be used, which will be adjusted for smoking status at baseline, based on the intention to treat (ITT) population. Testing will be hierarchical as described above with an overall level of significance of 5% (two-sided). All further analyses will be considered explorative.

Secondary analysis of the primary endpoint include models with adjustment for smoking status at baseline and other baseline variables in case of relevant imbalances between treatment groups. In addition, missing values will be imputed as sensitivity analyses. A per-protocol (PP) population will be defined and analyzed in a similar manner.

Secondary endpoints will be analyzed within similar frameworks as applicable.

All analyses will be specified in detail in a statistical analysis plan (SAP) which will be finalized prior to data analysis. Data analysis is conducted with the SAS for Windows, Version 9.3 or higher (SAS Institute, Cary, NC, USA) or other software.

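### Once the step-1 gate is passed, splitting alpha to 0.025 for each step-2 test protects nothing and costs about 11 points of power at the planned size

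*Protocol article*

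**What the plan says.** The testing order is set in the Protocol article, section Sample size determination. Step 1 compares Intervention 2 with control and acts as a gate: "Only if step 1 is significant at the 5% level (two-sided), will step 2 be tested confirmatively". Step 2 holds a pair of comparisons: "Intervention 1 (student smoking prevention circuit) compared to control; and Intervention 2 compared to Intervention 1, each with regard to the primary outcome". Alpha is divided between them: "with the two hypotheses tested equally (significance level alpha 0.025 each").

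The section Statistical analysis carries the scheme into the primary analysis: "Testing will be hierarchical as described above with an overall level of significance of 5% (two-sided"). No reason is given for dividing alpha after the gate. The three hypotheses are the three primary objectives listed under Objectives, and together they are all the pairwise comparisons of the three arms.

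**The concern.** A Bonferroni split guards against two true nulls being tested side by side. Here the three nulls are linked: if Intervention 1 equals control and Intervention 2 equals Intervention 1, then Intervention 2 equals control as well. So when the step-1 null is false, the two step-2 nulls cannot both be true. When the step-1 null is true, the gate already limits the error. The split therefore appears to correct for a situation that cannot arise.

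The price falls on two of the three primary objectives, including the added value of the parent component, which the Background and Discussion present as the gap in the evidence. It is also the step on which the trial was sized. Student recruitment fell short of the target (3023 against 3375), so power lost here cannot easily be regained by other means.

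**Working it through.** **Inputs** (Protocol article, Sample size determination). Assumed rates of regular smoking: control 35%, Intervention 1 30%, Intervention 2 25%. ICC 0.001, power 80%, 60 students per school, 15 schools per arm.

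**1. The plan's own figure.** The article states "15 (14.7 and 13.3 precisely for the two hypotheses) schools (=clusters) are required in each of the three arms". Design effect: 1 + (60 − 1) × 0.001 = 1.059. Schools per arm = (z_α/2 + z_0.80)² × [p₁(1−p₁) + p₂(1−p₂)] / 0.05² × 1.059 / 60.

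- At two-sided 0.025, (2.2414 + 0.8416)² = 9.505.
- 35% vs 30%: 9.505 × 0.4375 / 0.0025 = 1663 students; × 1.059 / 60 = 29.36 schools.
- 30% vs 25%: 9.505 × 0.3975 / 0.0025 = 1511 students; × 1.059 / 60 = 26.67 schools.

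The printed 14.7 and 13.3 are half of these (14.68 and 13.34). The halving is a separate problem, but the match shows that 0.025 was used as a two-sided level. A one-sided 0.025 would give 24.24 and 22.03, or 12.12 and 11.01 when halved, which does not fit.

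**2. Error control with 5% for each step-2 test.** Write C, I1 and I2 for the arms.

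- I2 = C true: a false step-2 claim requires a significant step 1, so the family-wise error is at most P(reject step 1) ≤ 5%, whatever level step 2 uses.
- I2 = C false: at most one of I1 = C and I2 = I1 is true. Only one false rejection is possible, and its probability is at most 5%.

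The two cases are exhaustive. This is closed testing with Shaffer's logical restrictions.

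Simulated family-wise error (normal approximation, 1,000,000 runs each, 15 × 60 per arm, ICC 0.001):

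| True state | 5% each | 2.5% each |
|---|---|---|
| All arms 35% | 0.050 | 0.050 |
| I1 = C = 35%, I2 = 25% | 0.049 | 0.024 |
| I1 = I2 = 25%, C = 35% | 0.049 | 0.024 |
| I2 = C = 35%, I1 = 30% | 0.050 | 0.050 |
| I1 = C = 35%, I2 = 5% | 0.050 | 0.025 |

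When exactly one step-2 null is true and step 1 has high power, the split leaves about half of the permitted error unused.

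**3. Power lost at the planned size.** Effective n per arm = 900 / 1.059 = 849.9. Power = Φ(z − z_α/2), with z = 0.05 / √([p₁(1−p₁) + p₂(1−p₂)] / 849.9).

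- I1 vs C: z = 0.05 / √(0.4375/849.9) = 2.204. At 0.025: Φ(2.204 − 2.241) = 48.5%. At 0.05: Φ(2.204 − 1.960) = 59.6%.
- I2 vs I1: z = 0.05 / √(0.3975/849.9) = 2.312. At 0.025: Φ(2.312 − 2.241) = 52.8%. At 0.05: Φ(2.312 − 1.960) = 63.8%.

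The gate takes almost nothing away, since step-1 power is about 99.5%. In the simulation at the assumed rates, the chance of rejecting both step-2 nulls rose from about 17% to 31%.

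**4. Sensitivity.** If power at 0.025 really were 80%, power at 0.05 would be Φ(2.2414 + 0.8416 − 1.960) = 86.9%, a gain of 6.9 points. With the arm sizes in Table 3 (1142, 980 and 679 students in 17, 16 and 14 schools), ICC 0.001 and 0 to 20% dropout, the loss is 10.4 to 11.1 points. For larger ICCs, which are assumptions and not in the article, the loss is about 10 to 11 points at 0.01, 9 to 10 at 0.02 and 7 to 8 at 0.05.

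**The case against.** The strongest reply is that nothing here is invalid. A 5% gate followed by two tests at 2.5% is a coherent procedure that controls the error strongly, and choosing it over a sharper one can be called a preference. It is true that the scheme is only conservative, and that limits the severity. But a preference normally trades one thing for another; here power is given up and no error control is gained.

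The 11 points also depend on a true power near 50%, which follows from the halved number of schools. That stands: the loss is about 7 points at the stated 80%. Nor does removing the split rescue step 2, where power stays at about 60% and 64%.

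The logical link requires the three nulls to concern one common set of arm parameters. Separate pairwise baseline-adjusted logit models need not give contrasts that add up exactly, and the article does not say whether one model or several will be used. This condition is real and belongs in the wording of the fix. Each mixed-model test must also hold its own level with 14 to 17 schools per arm, but that is needed at 2.5% as much as at 5%.

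Finally, raising a published threshold late in a trial can draw criticism, and the unseen SAP may already set other levels. Both are fair cautions. The article says the SAP will be finalised before data analysis, so the change can be prespecified with its justification.

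**Conclusion.** The concern holds. After a significant step 1, at most one step-2 null can be true, so testing both at two-sided 5% keeps the family-wise error at 5% in the strong sense. The split costs 11.1 points (59.6% to 48.5%) for Intervention 1 vs control and 11.0 points (63.8% to 52.8%) for Intervention 2 vs Intervention 1 at 15 × 60 per arm and ICC 0.001. The loss would be about 7 points if the stated 80% power were true.

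The error-control argument does not depend on the assumed rates or the ICC. It needs all three nulls to be stated for one set of arm parameters and each test to be valid at its own level. This is a loss of efficiency that should be corrected, not a failure of type I error control.

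**What to change.** Replace the split, in the SAP or by protocol amendment, with wording to this effect: if Intervention 2 vs control is significant at two-sided 5%, Intervention 1 vs control and Intervention 2 vs Intervention 1 are each tested at two-sided 5%; the family-wise error stays at 5% because at most one of these two nulls can be true when the step-1 null is false. State that all three contrasts come from one three-arm mixed model with the planned baseline adjustment.

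Date the change and finalise it before data analysis, and report it openly as a departure from the published levels. The cost is one or two sentences and the need to explain the change; the overall 5% level is unaffected. With recruitment closed, the benefit is in power: the lower requirement at 5% (24.2 rather than 29.4 schools per arm, and 22.0 rather than 26.7, about 17% fewer) only shows the size of the inefficiency.

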## Discussion

The BEST-Prevention study is among the largest randomized controlled trials in Germany that investigates the effectiveness of smoking prevention strategies among adolescents
[10]. It was designed to address important and unresolved issues in the context of behavioral smoking prevention strategies. Findings will be of importance for a number of reasons: Firstly, the BEST-Prevention study targets specific intervention components and addresses the additional effectiveness of a feasible parental smoking prevention strategy to reduce smoking rates among adolescents, which few studies have done so far
[11, 20]. Secondly, it targets adolescents at increased risk of smoking due to their diverse background and their residence in a large metropolitan area in Germany. Thirdly, this study assesses the long-term effectiveness of a smoking prevention intervention.

Despite recruitment challenges due to the implementation of a school reform in Berlin in 2010, which reduced the number of potentially eligible schools by about 50%, the targeted number of 45 schools and 161 school classes was achieved or even exceeded. However, with 3023 students meeting all selection criteria, the estimated sample size was not fully met.

Although our study did not aim to enroll a representative population of 7^th^ graders in Berlin we were able to recruit schools and students from all 12 districts of the city. This ensures that schools and students are located in districts and neighborhoods with diverse characteristics and SES. While we recruited schools, school classes and students from all these districts, the distribution of those does not fully reflect the general distribution across the city of Berlin. For instance, certain districts are overrepresented in terms of the relative number of schools and students enrolled, while others underrepresented. In terms of the type of school, there are 121 integrated secondary schools and 93 “Gymnasien” in Berlin. Within the BEST-Prevention study we enrolled 32 integrated secondary schools and 15 Gymnasien, reflecting a somewhat different distribution. Our population based sample in a major metropolitan area in Germany and its diversity will offer the opportunity to investigate the impact of various individual family characteristics, as well as neighborhood SES on smoking and other health behaviors. This will make findings highly relevant to populations which are frequently not adequately reached through prevention efforts.

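### The stated 15 schools per arm is about half of what the protocol's own inputs require, so step-2 power is about 48% and 53% instead of 80%; the ICC of 0.001 leaves no margin

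*Protocol article*

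**What the plan says.** Under *Sample size determination*, the Protocol article sizes the trial on step 2 of its hierarchy: Intervention 1 against control, and Intervention 2 against Intervention 1, "with the two hypotheses tested equally (significance level alpha 0.025 each"). The rates are "assumptions: intervention 1: 30%, intervention 2: 25%, and control group: 35" per cent. The clustering and power inputs are "an assumed intra-cluster correlation coefficient for schools (ICC) of 0.001 and a power of 80" per cent, with an average of 60 participating students per school. The result is "15 (14.7 and 13.3 precisely for the two hypotheses) schools (=clusters) are required in each of the three arms". The effect on which this rests is a 5-point difference in regular smoking at 24 months. That gives 2700 students, raised to 3375 for 20% drop-out.

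Under *Statistical analysis*, the models are fitted "with cluster effects (school and class within school"), and the primary logit model is adjusted for baseline smoking. Also there: "Testing will be hierarchical as described above with an overall level of significance of 5% (two-sided"). *Study design* states that school randomization was stratified by school type. Table 3 reports 59.6 ± 35.3 students per school and 17.4 ± 6.3 per class.

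**The concern.** There are two separate questions. The first is whether 15 schools per arm follows from the stated inputs. If not, the 80% power claim is wrong whatever the true ICC, and a null step-2 result (including the added value of the parent component) could be misread as the negative finding of a well-powered trial.

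The second is whether an ICC of 0.001 is a safe planning value. It gives a design effect of 1.06, so the trial is sized almost as if students had been randomized individually. Yet the *Discussion* stresses that "schools and students are located in districts and neighborhoods with diverse characteristics and SES", and the model carries a class level that the calculation does not mention. If between-school or within-class correlation is larger, power falls further.

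**Working it through.** **Inputs.** Rates 35%, 30% and 25%; alpha 0.025 per step-2 test, taken as two-sided in line with *Statistical analysis*; power 80%; ICC 0.001; m = 60; 15 schools, hence 900 students, per arm (all from *Sample size determination*). School size CV = 35.3/59.6 = 0.59 (Table 3).

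**1. The plan's own figure.** Students per arm: n = (2.2414 + 0.8416)² × [p1(1−p1) + p2(1−p2)] / (p1−p2)². Design effect: 1 + 59 × 0.001 = 1.059.

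- 35% v 30%: n = 9.505 × (0.2275 + 0.2100)/0.0025 = 1663; × 1.059 / 60 = 29.4 schools per arm.
- 30% v 25%: n = 9.505 × (0.2100 + 0.1875)/0.0025 = 1511; × 1.059 / 60 = 26.7 schools per arm.

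Halving the unrounded results gives 14.68 and 13.34, which are the stated 14.7 and 13.3. The pooled-variance formula gives n = 1667 and 1515, again 29.4 and 26.7 schools. Other readings do not give the stated pair per arm: alpha 0.05 two-sided (the same as 0.025 one-sided) gives 24.3 and 22.1; alpha 0.05 one-sided gives 19.1 and 17.4; m = 75 gives 23.8 and 21.6. The drop-out step is correct: 2700/0.8 = 3375.

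**2. Power at 15 × 60 per arm.** Power = Φ(d / √(sum of variances × DE / 900) − z).

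- 35% v 30%: 0.05/√(0.4375 × 1.059/900) = 2.204; Φ(2.204 − 2.241) = 48%.
- 30% v 25%: 0.05/√(0.3975 × 1.059/900) = 2.312; Φ(2.312 − 2.241) = 53%.
- With ICC 0 (DE = 1): 51% and 55%.
- Step 1, 35% v 25% at alpha 0.05: 0.10/√(0.4150 × 1.059/900) = 4.525; Φ(4.525 − 1.960) is above 99%.
- Difference detectable from 35% with 80% power: at d = 0.069 the variances sum to 0.4295, and 3.083 × √(0.4295 × 1.059/900) = 0.069, so about 7 points.

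**3. What ICC 0.001 implies.** The between-school SD is √(0.001 × 0.30 × 0.70) = 1.45 points at 30% and 1.51 at 35%, so about 95% of schools lie within 3 points of the mean. With the student split of 41.9/58.1 in Table 3, a 3-point gap between school types alone gives 0.419 × 0.581 × 0.03²/0.21 = 0.00104 (0.00096 at 35%). With the 32:15 school split, 3.1 points are needed. A 10-point gap would give about 0.010 to 0.012.

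**4. Sensitivity.** DE = 1 + ((1 + CV²)m − 1) × ICC with CV 0.59, 15 × 60 per arm. ICCs above 0.001 are assumptions.

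| ICC | DE | 35 v 30, alpha 0.025 | 35 v 25, alpha 0.05 |
|---|---|---|---|
| 0.001 | 1.08 | 48% | 99% |
| 0.01 | 1.80 | 29% | 93% |
| 0.02 | 2.60 | 20% | 82% |
| 0.05 | 5.00 | 11% | 55% |

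Size variation alone costs about 1 point of power at ICC 0.001 (DE 1.059 to 1.080). An assumed additional class ICC of 0.01 or 0.05, with DE = 1 + 16.4 × class ICC + 0.059, gives DE 1.22 or 1.88 and power of 42% or 28% for 35% v 30%.

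**The case against.** The best defence concerns the ICC. The article gives no smoking rates by school type, so every gap above is hypothetical. School type is a stratification factor, which largely balances it across arms, and its variance leaves the school effect if the model adjusts for it. Baseline smoking may absorb more. A school ICC defined as the average correlation within a school already includes class clustering, so the lack of a separate class term is not in itself an error. An article need not cite a source for its ICC. Wanting to study neighbourhood SES as a moderator concerns varying effects, not a larger outcome ICC. All of this stands, and it makes the ICC part conditional. As described, however, the primary model names only baseline smoking as a covariate.

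A reader might infer that the optimistic ICC is why 80% power fails. The figures do not support this: with no clustering at all, power is still only 51% and 55%. A sponsor could justify 0.001 fully and the shortfall would remain. A reader might also infer that the gatekeeper test is undermined. At the planned size it keeps 82% or more up to an assumed ICC of 0.02, and nothing in the article shows that larger values apply.

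Against the factor of two, one could argue that baseline adjustment recovers precision. It would have to cut the variance by about half (15/29.4 = 0.51), and the plan claims no such gain.

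**Conclusion.** The schools-per-arm figure is an arithmetic error of a factor of two at the protocol's own inputs. It rests on no outside assumption beyond standard normal-approximation formulas and a two-sided test. The design delivers about 48% and 53% power for the two step-2 comparisons; step 1 is not affected.

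The ICC of 0.001 is fragile, but it is a secondary matter. That a 3-point school-type gap would produce it is exact arithmetic; that such a gap exists, or remains after adjustment, is not shown. The further losses, to 29% and 20% for 35% versus 30%, hold only under the assumed ICCs of 0.01 and 0.02 with CV 0.59. Step 1 falls below 80% at the planned size only at ICCs above 0.02 (55% at 0.05).

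**What to change.** - Correct the requirement to 29.4 and 26.7 schools per arm, and withdraw the statement that 15 schools per arm give 80% power.
- State step-2 power at 15 × 60 per arm and ICC 0.001 as about 48% and 53%, with a detectable difference of about 7 points from 35%.
- Add a sensitivity range for steps 1 and 2 over ICC 0.001 to 0.05, using DE = 1 + ((1 + CV²)m − 1) × ICC. Inform it with school and class ICCs estimated from the 12-month smoking data with arms masked, adjusted for school type and baseline smoking. Fix it before the 24-month analysis.

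The cost is a short masked calculation and a less favourable stated power. No new students or data are needed.

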### Study design

This study is a three-armed parallel cluster randomized controlled trial among secondary schools with 7^th^ grade classes. As the unit of randomization schools were randomly assigned using a 1:1:1 ratio and a blocked randomization with variable block length, stratified by school type (Gymnasium vs. integrated secondary school) to one of three intervention groups. The randomization sequence was generated using central computer generated randomization lists and allocation was concealed from participating schools.

Intervention 1:student smoking prevention circuitIntervention 2:student smoking prevention circuit plus parent interventionControl group:student nutrition and physical activity circuit (without smoking prevention)

Given the nature of the intervention, schools and study participants are not blinded to the assigned intervention. However, data analysis of follow-up outcomes will be blinded with regard to the intervention group.

Data collection for each student is conducted at three different time points, including baseline (at the beginning of the 7^th^ grade school year), follow-up 1 (12 month) and follow-up 2 (24 month) (Figure 
1). Prior to baseline data collection one additional visit was performed in all school classes in order to inform students about the study and to distribute participant information and consent forms.

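### The planned 15 schools per arm is half of what the stated inputs require: the two step-2 tests have about 50% power, not 80%

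*Protocol article*

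**What the plan says.** The protocol article, under Sample size determination, sets up two steps. Step 1 compares the combined student-parent intervention with control. If that is significant, step 2 tests the student intervention against control and the combined intervention against the student intervention, "with the two hypotheses tested equally (significance level alpha 0.025 each". The section bases the sample size on step 2 because its assumed effects are smaller.

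The inputs are all printed:

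- the expected proportions of regular smokers at two years ("assumptions: intervention 1: 30%, intervention 2: 25%, and control group: 35"%)
- the "assumed intra-cluster correlation coefficient for schools (ICC) of 0.001 and a power of 80"%
- the cluster size ("Since we assume on average 60 participating students per school")

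The Statistical analysis section adds: "Testing will be hierarchical as described above with an overall level of significance of 5% (two-sided"). The Study design section says that "schools were randomly assigned using a 1:1:1 ratio".

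The result is that "15 (14.7 and 13.3 precisely for the two hypotheses) schools (=clusters) are required in each of the three arms to detect a 5% difference". It is then used as a per-arm number: 15 × 3 × 60 = 2700 students, raised to 3375 for 20% drop-out.

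**The concern.** A 5-point difference between proportions near 30%, tested at two-sided 0.025 with 80% power, needs well over 1,000 students per arm even before clustering. The plan has 900 per arm after clustering. Because every input is printed, the result can be checked directly.

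Step 2 carries two of the three primary objectives, including the added value of the parent component, which the Background and Discussion present as the main gap in the evidence. If the trial is believed to have 80% power for these contrasts when it has about 50%, a non-significant result is easily taken as evidence that the circuit, or the parent component, does not work. The Discussion also measures recruitment against the target of 45 schools and reports it as met or exceeded, which reinforces the impression that the design is close to its stated power.

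**Working it through.** **Inputs.** All are from Sample size determination except the two-sided level (Statistical analysis) and equal allocation (Study design).

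- Rates: control 35%, student intervention 30%, combined intervention 25%
- Two-sided alpha 0.025 per hypothesis: z = 2.2414
- Power 80%: z = 0.8416
- (2.2414 + 0.8416)² = 9.505
- Design effect: 1 + (60 − 1) × 0.001 = 1.059

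**Required schools per arm.** Students per arm before clustering: n = 9.505 × [p₁(1−p₁) + p₂(1−p₂)] / 0.05². Schools per arm: n × 1.059 / 60.

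| Contrast | Sum of variances | n per arm | × 1.059 | Schools per arm | Half | Printed |
|---|---|---|---|---|---|---|
| 35% vs 30% | 0.2275 + 0.2100 = 0.4375 | 1663 | 1761.5 | 29.36 | 14.68 | 14.7 |
| 30% vs 25% | 0.2100 + 0.1875 = 0.3975 | 1511 | 1600.5 | 26.67 | 13.34 | 13.3 |

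The plan's figures are therefore reproduced only after dividing the correct per-arm number by two. The pooled-variance formula gives 29.42 and 26.74, with halves of 14.71 and 13.37.

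**Other readings of the inputs.** None gives 14.7 and 13.3 as per-arm numbers:

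| Reading | 35% vs 30% | 30% vs 25% |
|---|---|---|
| Two-sided 0.05 (no alpha split), same as one-sided 0.025 | 24.2 | 22.0 |
| One-sided 0.05 | 19.1 | 17.4 |
| One-sided 0.10 | 13.9 | 12.7 |
| No clustering (ICC 0) | 27.7 | 25.2 |
| 75 students per school | 23.8 | 21.6 |
| 120 students per school | 15.5 | 14.1 |

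Drop-out does not explain the gap, because it is added after the 2700.

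**Power at the planned size.** With 15 × 60 = 900 analysed students per arm, power = Φ(0.05 / SE − 2.2414), where SE = √(sum of variances × 1.059 / 900).

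- 35% vs 30%: SE = 0.02269; Φ(2.204 − 2.241) = 48.5%
- 30% vs 25%: SE = 0.02163; Φ(2.312 − 2.241) = 52.8%

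Using a t reference with 28 degrees of freedom for the 30 schools in each contrast lowers these to about 45% and 49%.

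**Detectable difference.** At 900 per arm, 80% power is reached for a drop of 6.9 points from 35%, or 6.6 points from 30%.

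**Size that would give 80%.** Rounding 29.4 up gives 30 schools per arm: 30 × 3 × 60 = 5400 analysed students, or 5400 / 0.8 = 6750 with the assumed drop-out.

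**Step 1.** For 35% vs 25% at two-sided 0.05, about 5.8 schools per arm suffice, and power at 15 is about 99%.

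**Students actually enrolled.** Table 3 gives 1142 (student), 980 (combined) and 679 (control) at baseline. With the mean school sizes in that table, the same ICC and the same rates, power is about 46% for student against control and 60% for combined against student. If the assumed 20% drop-out then applied, it would be about 37% and 50%.

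**The case against.** The arithmetic itself cannot be defended, but several qualifications are fair.

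- **Exactness and mechanism.** The halving matches both printed decimals only with the unpooled variance; with the pooled formula the second figure would print as 13.4. The section names no formula or software, so the lost factor of two is an inference. Neither point changes the required number of schools.
- **Covariate adjustment.** The primary model adjusts for baseline smoking, which may change power. To restore 80% at 900 per arm, it would have to cut the variance to 900 / 1761.5 = 51% of its unadjusted value for the first contrast, and to 900 / 1600.5 = 56% for the second. The section claims no such gain, and the match with half the unadjusted figure suggests that none was used.
- **Planned against actual size.** The 48% and 53% refer to the planned size under the stated assumptions. Actual enrolment differs by arm, but it does not bring either contrast to 80%.
- **Practical weight.** Recruitment is complete, type I error is unaffected and step 1 is well powered. The error does not bias any estimate. That a null result will be misread is a risk, not something the document commits to. This limits the remedy to corrected text; it does not make the stated power right.

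**Conclusion.** The concern holds. On the section's own inputs, 29.4 and 26.7 schools per arm are needed, about twice the printed 14.7 and 13.3. At 15 schools of 60 analysed students per arm, power for the two step-2 contrasts is about 48% and 53% instead of 80%, and the difference detectable with 80% power is 6.6 to 6.9 points instead of 5. These figures assume the stated rates, an ICC of 0.001, equal schools of 60 and an unadjusted comparison. They are per hypothesis; the chance that both tests succeed is lower. This must be corrected, because the stated power is wrong for two of the three primary objectives. The first-step comparison stands.

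**What to change.** Correct the Sample size determination section to say that 80% power requires 29.4 and 26.7 schools per arm for the two step-2 hypotheses. State that 15 schools of 60 students per arm give about 48% and 53% power, with a detectable difference of about 7 points at 80% power, and that step 1 keeps about 99%. If the sponsor relied on a gain from baseline adjustment, that gain and its source should be stated.

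The SAP, which the article says will be finalised before the data are analysed, and the results paper should state that a non-significant step-2 contrast is inconclusive and is interpreted from its confidence interval.

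The cost is corrected text and a less favourable statement of power. The design, the test hierarchy and enrolment need not change.

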## Conclusion

In summary, the present manuscript provides an overview of the study design and methodology of a large school-based smoking prevention cluster randomized controlled trial in a metropolitan area in Germany. Recruitment of the BEST-prevention study was successful in enrolling targeted numbers of schools and school classes, although the number of students was somewhat lower than planned. Moreover, enrolled schools and students represent all districts of the city. Findings from our study will soon provide valuable information with regards to the acceptability and effectiveness of specific smoking prevention strategies also in disadvantaged population groups. Furthermore, the additional effectiveness of strategies targeting parents will be determined.

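### The inflation to 3,375 students for drop-out is not reconciled with 60 students per school and 45 schools, and recruitment against target is not shown by arm

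*Protocol article*

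**What the plan says.** All references are to the protocol article.

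- **Sample size determination.** Step 2 sets the size, "with the two hypotheses tested equally (significance level alpha 0.025 each". The inputs are an "intra-cluster correlation coefficient for schools (ICC) of 0.001 and a power of 80"%, and "assumptions: intervention 1: 30%, intervention 2: 25%, and control group: 35"%. The result is 15 schools in every arm (14.7 and 13.3 before rounding). The student count follows: "Since we assume on average 60 participating students per school", the requirement is 15 × 3 × 60 = 2,700. Then: "Assuming a drop-out rate of about 20% this yields a targeted sample size" of 3,375. Neither the number of schools nor the number per school is restated after this step.
- **Discussion.** "the targeted number of 45 schools and 161 school classes was achieved or even exceeded". The next sentence says that the student target was not fully met, with 3,023 students.
- **Conclusion.** It repeats that school and class recruitment succeeded and adds that "the number of students was somewhat lower than planned".
- **Results and Table 3.** Two schools withdrew after allocation to control. The remaining 47 schools divide 17 / 16 / 14 (student / student-parent / control). Students with a baseline questionnaire divide 1,142 / 980 / 679, total 2,801. The control mean is 48.5 per school and the overall mean 59.6.

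**The concern.** The 2,700 is built from schools times students per school, so a change to the total must show up in one of the two factors. The text changes the total and leaves both factors as they were. A reader cannot tell whether the trial was to recruit 75 students from each of 45 schools, or whether the drop-out allowance was never turned into a recruitment target.

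The same gap affects the account of recruitment. The requirement is set per arm, but achievement is reported for all arms together. Control enters two of the three primary comparisons and is the smallest arm. The pooled wording does not show how far it is below plan. The only power figure in the article is 80%, and a non-significant step 2 result would be read against it.

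**Working it through.** **Inputs.** From Sample size determination: rates 35%, 30%, 25%; ICC 0.001; power 80%; alpha 0.025 per step 2 hypothesis, taken as two-sided because step 1 and the overall level are; 60 per school; drop-out 20%. From the Discussion: 45 schools. From Results and Table 3: achieved counts, means and SDs.

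**1. Drop-out step.** 2,700 / (1 − 0.20) = 3,375. The stated figure reproduces exactly.

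**2. What 3,375 implies.**
- At 45 schools: 3,375 / 45 = 75 enrolled per school.
- At 60 enrolled per school: 3,375 / 60 = 56.25 schools, more than 45.
- At 45 schools and 60 enrolled: 2,700 enrolled; 60 × 0.8 = 48 and 2,700 × 0.8 = 2,160 analysed, 20% below the requirement.

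**3. Achieved per school.** Baseline data: 2,801 / 47 = 59.6. Consented: 3,023 / 47 = 64.3.

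**4. Control against target.** Per arm the plan implies 15 × 60 = 900 required and 3,375 / 3 = 1,125 enrolled.
- 679 against 900, before drop-out: 24.6% short.
- Consented control students are not given in the text. Scaling by the overall ratio (an assumption): 679 × 3,023 / 2,801 ≈ 733, against 1,125: 35% short.
- 679 against 1,125: 39.6% short.
- 679 × 0.8 = 543 against 900: 39.6% short.

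**5. School count, to separate the two problems.** Schools per arm = (z₀.₉₈₇₅ + z₀.₈₀)² × [p₁(1−p₁) + p₂(1−p₂)] / 0.05² × [1 + (m−1) × 0.001] / m, with (2.241 + 0.842)² = 9.505.
- m = 60: 1,663.4 × 1.059 / 60 = 29.36 (35% vs 30%) and 1,511.3 × 1.059 / 60 = 26.67 (30% vs 25%). The stated 14.7 and 13.3 are half of these (14.68 and 13.34).
- m = 48: 36.28 and 32.97; their halves are 18.14 and 16.48. So even on the plan's halved scale, 15 schools are too few if 60 is the enrolled number.

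**6. Power as planned.** At 15 × 60 = 900 per arm, the effective n is 900 / 1.059 = 849.9, and power is about 48% and 53%, not 80%.

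**7. Power as achieved.** Power = Φ(|p₁−p₂| / SE − z), where each arm's n is divided by 1 + ((1 + CV²)m − 1) × 0.001. With 20% off the baseline counts and CVs from Table 3:
- Effective n: student 913.6 / 1.068 = 855; student-parent 784 / 1.067 = 735; control 543.2 / 1.053 = 516.
- Intervention 1 vs control: SE = √(0.21/855 + 0.2275/516) = 0.0262; Φ(0.05/0.0262 − 2.241) ≈ 37%.
- Intervention 2 vs Intervention 1: SE = √(0.1875/735 + 0.21/855) = 0.0224; power ≈ 50%.
- Step 1, alpha 0.05: SE = √(0.1875/735 + 0.2275/516) = 0.0264; Φ(0.10/0.0264 − 1.960) ≈ 97%.

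Taking 20% off the scaled consented counts instead (986 / 846 / 586) gives about 40%, 53% and 98%.

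**The case against.** The strongest reply is that 60 may mean analysed students. The text calls 2,700 the requirement and inflates afterwards, so 75 enrolled in each of 45 schools is coherent, and losing students does not by itself call for more schools. This stands. It means that the text is unreconciled, not that the arithmetic is proved wrong. The achieved 59.6 per school cannot settle what the planners meant.

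Three stronger readings are tempting and are not supported.

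- *That the trial should have had 57 schools.* This takes 60 as the enrolled number and keeps the halved school count. Nineteen schools per arm with 48 analysed would still give only about 50% and 54% power.
- *That the article conceals the shortfall.* Only the school and class targets are called met, and 47 against 45 is true. The student shortfall is stated in the Discussion and the Conclusion, Table 3 prints the control figures, and both withdrawals are reported. Adding those two schools to the 14 gives 16 randomized to control, so 15 per arm was reached at allocation and lost afterwards.
- *That control is simply 40% short, and that this explains the low power.* The 40% either sets baseline completers against an enrolment target or takes 20% off a count that already excludes 222 of the 3,023 consented students. Completers are still a defensible basis, because the primary model adjusts for baseline smoking. The shortfall matters materially for one comparison only, Intervention 1 against control; step 1 stays at about 97%.

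**Conclusion.** The concern holds in a limited form. The section on sample size and the Discussion leave 60 against 75 students per school open; under one reading the analysed total falls to 2,160, under the other an enrolment of 75 per school was needed and not approached. Control retained 14 of the 15 schools required and is 25% to 40% below its student target, depending on which counts are compared; the 35% figure in between rests on assumed proportional scaling of consent.

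The stated 80% does not describe the trial as recruited. On the plan's own rates, ICC and 20% drop-out, step 2 power is about 37–40% and 50–53%. Most of that gap is already present at the planned 15 × 60 (48% and 53%) and belongs to the separate halving of schools per arm. The recruitment shortfall then takes 8 to 11 points from Intervention 1 against control and 0 to 3 from Intervention 2 against Intervention 1. These figures assume the ICC of 0.001 and equal drop-out across arms.

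**What to change.** 1. In Sample size determination, say whether 60 is the enrolled or the analysed number per school, and give school and per-school targets that agree with 3,375.
2. In Results or the Discussion, tabulate target against achieved by arm on a like-for-like basis: schools 15 against 17 / 16 / 14, with the two control withdrawals noted; consented students against 1,125; students with baseline data against a target defined at the same stage; and, when known, analysed students against 900. Reword the Discussion and Conclusion to match.
3. Replace the 80% with achieved power or detectable difference for each of the three comparisons, computed after the school formula is corrected.

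The cost is a text correction, one small table and a short calculation. Consented counts by arm should already be in the trial records. No new enrolment and no change to the design are needed.
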